### Sample size determination

The results of the above-mentioned pilot study (Koller et al. [33]) included a maximum mean alleviation of 0.99 NRS (0–10) for average pain and a mean alleviation of 1.27 NRS (0–10) for the worst pain compared to the control group in week nine. For these two endpoints, based on average pain improvement data, an alpha error of 0.05 (95%) and a beta error of 0.2 (80%) would require a 136-patient sample to achieve sufficient statistical power. Estimating an attrition rate of 35% over the 6-week study period, it will be necessary to recruit a total sample of 210 patients. We expect to recruit 50% of patients along with FCs. This number will be sufficient. Based on Wells, Hepworth, Murphy, Wujcik, and Johnson [40], who assessed initial effects of an intervention to increase knowledge and positive beliefs about cancer pain management in patients using the Family Pain Questionnaire (FPQ), an improvement in knowledge and beliefs were found [F (1,62) = 18.2, *p* < 0.001]. At an alpha error level of 0.05, a sample size of 32 FCs should be sufficient to achieve a statistical power of 80%.

With respect to the sample size for the qualitative part, a sample of 42–60 patients and FCs should supply sufficiently redundant data to discover patterns, commonalities and differences among the groups.

### Recruitment

Specifically trained nurses from the outpatient clinics work as research assistants (RAs) for the study. All RAs are experienced registered nurses or graduate students in nursing who have received study-specific training by the study coordinator (HR). RAs screen potential participants and verify inclusion criteria via patient files and discussions (regarding life expectancy, etc.) with their treating physicians. If the initial inclusion criteria are met, the RAs contact the patients directly during their outpatient appointment to check whether they have experienced repeated pain that they would rate on an NRS as ≥3 over the last week, are able to understand, read and write German, and have access to a telephone. The RAs then inform patients about the study and invite them to participate. Each patient is also asked if an FC is involved in their daily pain self-management. If yes, the FC is also invited to participate in the study. Written information and consent forms (including those for FCs, if necessary) are then given to the patient. After at least 24 h, an RA contacts each patient (or patient/FC dyad) again to provide verbal information to the FC as needed, ask about their decision regarding participation, and collect the signed written consent form. In all settings, these written informed consent forms are stored safely in the Investigator Site File (ISF) by the RAs. Only afterwards are participants randomized to the IG or CG. Patients and FCs have the right to withdraw from the study at any time without consequences.

Concerning the recruitment of participants for qualitative data collection, all patients (and FCs) are asked at the beginning of the main study whether they are willing to participate in an interview following completion of the study’s 6 weeks of procedures. At the end of the final home visit, the intervention nurse (IN) or an RA asks selected patients (and FCs) whether they are still willing to participate in the interview. They then provide verbal and written information and obtain written consent from those who agree. Purposive sampling is applied to ensure approximately equal sample sizes per study site, as well as variation regarding pain intensity, intervention adherence, age, gender, education, living situation, and tumour entity.

### Random assignment

As shown in Fig. 2, patients and FCs who have provided written consent are stratified by site and randomized 1:1 either to a six-week intervention group (IG) or to a usual care group (CG). A permuted block procedure, with blocks of 2, 4 and 6, is used to create a computer generated randomization list. This procedure should ensure approximately equal distribution of patients per group and per centre. The Clinical Trial Unit (CTU) of one of the included university hospitals provides the list, which is accessible from all settings.

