### Blinding

Blinding is not possible because the INs use collected data directly for the intervention (pain diary, Patient Pain Questionnaire (PPQ)). And while treating physicians are not informed, they may still become aware of group allocation if participants ask questions or take their diary to an appointment.

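### As worded, the protocol makes the randomisation list itself accessible at the recruiting sites of an unblinded trial, so allocation concealment is not assured

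*Protocol article*

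**What the plan says.** Under Random assignment, participants are stratified by site and allocated 1:1. The sequence is described thus: "A permuted block procedure, with blocks of 2, 4 and 6, is used to create a computer generated randomization list". The next but one sentence deals with access: "The Clinical Trial Unit (CTU) of one of the included university hospitals provides the list, which is accessible from all settings".

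Under Recruitment, the recruiters are clinic staff: "Specifically trained nurses from the outpatient clinics work as research assistants (RAs) for the study". They exercise judgement before enrolment: "RAs screen potential participants and verify inclusion criteria via patient files and discussions (regarding life expectancy, etc.) with their treating physicians". They then check pain level and language with the patient, give the invitation, ask whether an FC is involved and invite that FC too. After at least 24 hours they return for the decision and the signed consent. Randomisation comes after consent.

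Under Blinding: "Blinding is not possible because the INs use collected data directly for the intervention". Under Data collection, an RA collects the control-group data and the intervention nurse collects the intervention-group data.

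**The concern.** The object made accessible is the list, not a single assignment or an allocation service. No role restriction and no one-at-a-time release is attached to it. The people who decide whom to screen, invite and enrol, and when, work at the places from which it can be reached.

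An RA who can see the next entry can, without any intent to mislead, delay a frail patient, bring forward a motivated dyad, or put less effort into finding an FC when the next slot is usual care. FC participation is particularly exposed:

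- it is optional and settled before allocation;
- eligible FCs must be willing to attend all intervention sessions;
- half of the patients are expected to bring one (0.5 × 210 = 105);
- FC knowledge is a primary outcome.

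The outcomes compared between arms (side effects, knowledge) are self-reported. Arms that differ at entry in severity or motivation would therefore produce differences that look like an intervention effect.

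**Working it through.** **Step 1. Does the text put the list within reach of the recruiters?**

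- *Where the list can be reached:* all settings (Random assignment).
- *What a setting is:* Recruitment uses the same expression for the places where RAs file the consent forms, so the settings are the study sites.
- *Who works there:* clinic nurses acting as RAs, who screen, invite and consent (Recruitment).
- *What limits access:* nothing stated.
- *Are past allocations visible?* Yes. The trial is unblinded, and data collection is split by arm between the RA and the intervention nurse.

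Followed literally, the rule lets a recruiter know the next assignment before enrolment.

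**Step 2. Does consent before randomisation close the gap?** No. It fixes the order of events for a given participant. It does not govern which patients are approached, whether an FC is sought, or on which day a consent is collected and the patient entered.

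**Step 3. How predictable is the next assignment?** The protocol gives no figure for this, so there is none to reproduce.

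*Future entries visible:* 100%. This follows from the reading of the access sentence and is not an independent measurement.

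*List closed, past allocations at the site known:* the best simple strategy is to guess the arm that is behind. For a block of size 2m, the expected number of correct guesses (Blackwell–Hodges) is

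m + 2^(2m−1) / C(2m, m) − 1/2.

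| Block size | Expected correct | Share |
|---|---|---|
| 2 (m = 1) | 1 + 2/2 − 0.5 = 1.5 | 1.5/2 = 75.0% |
| 4 (m = 2) | 2 + 8/6 − 0.5 = 2.833 | 2.833/4 = 70.8% |
| 6 (m = 3) | 3 + 32/20 − 0.5 = 4.1 | 4.1/6 = 68.3% |

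The protocol does not give the frequency of each block size. Assuming equal frequency:

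- sizes 2, 4 and 6: (1.5 + 2.833 + 4.1)/12 = 8.433/12 = 70.3%;
- sizes 4 and 6 only: (2.833 + 4.1)/10 = 6.933/10 = 69.3%.

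Dropping size 2 therefore gains 70.3 − 69.3 = 1.0 percentage point.

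**Step 4. Simulation check.** The assumptions were 70 patients per site (210/3, equal recruitment at the three sites), equally frequent block sizes and 4,000 runs. An observer who knows the set of sizes and the full site history guesses 70.1% correctly, in agreement with step 3. About 4% of assignments are certain if individual block sizes are unknown. About 32% are certain if each block's size is known. Not disclosing block sizes therefore matters more than removing the smallest one.

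**The case against.** The best defence is that the sentence is loosely worded. A CTU list that can be reached from three hospitals also fits a central web service that shows one assignment at a time. The article does not say who may open the list, whether future entries are visible, or that RAs consult it. A condensed article may also leave access rights to the full protocol. This defence stands in part. A reader might infer that allocation was in fact unconcealed and that recruiters knew every assignment; the text does not establish either. But the point does not rest on silence. The article states that the list itself is accessible at the sites, and that rule as written does not protect concealment.

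Second, at least 24 hours pass between invitation and the consent contact, and another patient may take the open slot meanwhile. That makes steering at first approach less certain. It leaves control over whom to enrol, and when.

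Third, varied block sizes are themselves a guard against prediction. Agreed. A reader might infer from the block of 2 that the blocking scheme is faulty, but step 3 shows that removing it changes little. The 70% also supposes someone who tracks every allocation at a site.

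Fourth, the models control for age, education, time since diagnosis and disease status, with anxiety, depression, functional status and cancer-related symptoms as covariates. This deals with part of any measured imbalance, but not with unmeasured differences such as motivation.

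**Conclusion.** The point holds as a fault in the stated procedure: concealment is not assured by the wording, and on its plain reading upcoming assignments are open to recruiting staff. The correction is needed because the efficacy comparisons depend on concealment.

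Its reach is the between-arm comparisons of aims 1 and 2. A reader might extend it to every result of the study. That goes too far, because aim 3 rests on correlations and qualitative work and makes no randomised efficacy claim.

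The size depends on the reading. Predictability is 100% if future entries are visible. It is about 70% with the list closed and the site history tracked, under equal block frequencies. The size of any resulting bias cannot be derived from the document.

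**What to change.** Replace the access sentence under Random assignment with, for example:

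> *The list is held by the CTU and is not visible to recruiting site staff. A single assignment is released, through the trial database or by the CTU, only after eligibility and written consent of the patient (and of the FC, if applicable) have been irrevocably recorded. Block sizes are not disclosed to site staff.*

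If practice already works this way, only the sentence needs correcting. If not, the cost is a change of access rights and a few minutes per randomisation. The blocks of 2, 4 and 6 may stay.

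The release condition is deliberately limited to eligibility and consent. The abstract places randomisation after baseline evaluation, whereas Data collection has arm-specific staff collecting data, including at the baseline visit. Making baseline data a condition of release would first require those two statements to be reconciled.

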**Fig. 2 Fig2:**
[figure not shown]
Flow chart of patient recruitment. Note. Flow chart of patient recruitment

### Blinding

Blinding is not possible because the INs use collected data directly for the intervention (pain diary, Patient Pain Questionnaire (PPQ)). And while treating physicians are not informed, they may still become aware of group allocation if participants ask questions or take their diary to an appointment.

### Intervention group and usual care group

#### Intervention group

The intervention is performed by four specially trained oncology nurses. These INs have completed a Master’s degree in nursing and are experienced clinicians in this field of study. A two-day training segment provided by the primary investigator (ES) included a review of current pain management guidelines and detailed teaching and training for each intervention component of the adapted German PRO-SELF © Plus PCP.

The intervention is intended to implement structured and tailored components of the German PRO-SELF© Plus PCP and is based on three key strategies: nurse coaching, skill building, and provision of information via academic detailing [30, 41]. Academic detailing focuses on enhancing baseline knowledge by providing key information and positive reinforcement, while stimulating the learner as an active partner [42, 43]. Structured intervention components focus on patients’/FCs’ education to monitor pain and analgesics’ side effects (e.g., nausea, emesis, constipation, concentration difficulties, fatigue), to document analgesics taken, and to use a one-week pillbox. They are also trained to apply a script to communicate with clinicians when pain control is inadequate.

To identify patients’ and FCs’ pain management knowledge deficits, the INs check their baseline knowledge of cancer pain and side effect management based on the results of the PPQ. To reinforce their education and enhance knowledge of cancer pain and side effects, patients and FCs receive the PRO-SELF © Pain Control Booklet, as well as individualized information.

Concerning the tailored intervention components, the IN reviews each pain diary with the associated patient/FC, assesses the appropriateness of the analgesic prescription and the side effect management, and teaches the patient/FC how to adjust the prescribed analgesics in response to changing pain conditions and side effects. Adherence to analgesic medication instructions and the IN’s recommendations is assessed and discussed with the patient/FC at each subsequent visit, after which modifications to the pain and side effect management plan are made as needed. The intervention is provided during in-home visits (baseline, weeks 1 and 6), followed by weekly in-home or telephone visits. The number, type (in-home visit or phone call) and frequency of visits are determined by defined criteria as follows: pain score > 3 on an NRS, patient is dissatisfied with pain management, patient adherence with pain medication or recommendations < 50%. If one or more of these criteria apply, the IN schedules an in-home visit; if none apply, she schedules a phone call. In addition, a reinforcement phone call is scheduled after major changes to the pain management plan.

For quality assurance and analysis, all intervention sessions and phone calls are audio recorded. The primary investigator and the study coordinator review audio recordings of visits and report their observations using an audit checklist based on the intervention protocol. In order to enhance the intervention’s implementation, they and the INs promptly discuss any deviations. They continue to monitor audiotapes until a 95% protocol adherence rate is achieved. Afterwards, audio-recordings are reviewed at random.

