**Discussion:**

In clinical practice, specially trained oncology nurses in outpatient clinics could apply the intervention to reduce side effects and to enhance patients’/FCs’ self-efficacy and pain management knowledge.

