### Data collection

Both quantitative and qualitative data will be collected from March 2016 until December 2018. Patients in both groups complete a daily pain and symptom diary; patients and FCs fill in questionnaires. The same 6-week data collection protocol is applied via in-home visits at baseline and during weeks 1 and 6. In the IG, data are collected by the IN. In order to minimize diffusion of the intervention to CG participants, an RA collects data in the control group. Between in-home visits at baseline and weeks 1 and 6, patients/FCs receive brief telephone calls every second week, during which the RA ensures that the pain diary is being completed on a daily basis.

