### Data analysis

Quantitative data will be compiled and analysed using SPSS 24.0. Data will be retrieved from the SecuTrial® database. Data will be systematically examined for out of range values and data inconsistencies. As appropriate, descriptive statistics will be calculated, including means and standard deviations for interval variables and frequencies, as well as percentages for categorical variables. An intent-to-treat analysis will be applied, using a significance level of .05 [55]. Although premature withdrawal is expected to be a random process, participants who completed the study will be compared with those who did not based on demographics, treatment group and other salient variables.

#### Data analysis for aim 1

Generalized linear mixed models will be applied to determine differences between the IG and the CG analgesic side effect developments throughout the intervention. This approach allows calculation of the main group and time effects, and of group-by-time interaction. The influence of missing data on the model results will be examined using sensitivity analysis [56]. Change scores for each patient as well as Cohen’s d will be calculated for each variable of interest.

#### Data analysis for aim 2

Our quantitative analysis will use descriptive statistics to summarize PPQ/FPQ items’ distribution characteristics. Generalized linear mixed models will be applied to determine differences between the IG’s and the CG’s knowledge of cancer pain management throughout the intervention. The influence of missing data on the model results will be examined using sensitivity analysis [46]. Change scores for each patient/FC as well as Cohen’s d will be calculated for each variable of interest.

For qualitative data analysis, transcript data will be stored and analysed in ATLAS.ti 7. Field notes and audiotapes of telephone calls, home visits and interviews will serve as qualitative data to explore both the IG’s and the CG’s the learning processes concerning knowledge of cancer pain and pain self-management. Data will be analysed via interpretive description–an approach using stepwise, systematic and iterative processing of data to arrive at a meaningful description and interpretation [57].

Information from quantitative and qualitative data collection will be combined within a mixed method matrix. Qualitative and quantitative results related to each German PPQ/FPQ item will be integrated in a final synthesis [39, 58].

#### Data analysis for aim 3

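### Four nurses deliver the intervention in one arm only, yet the sample size states no allowance for nurse clustering and the analysis names no nurse effect

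*Protocol article*

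**What the plan says.** All references are to the protocol article.

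- **Delivery.** Under Intervention group: "The intervention is performed by four specially trained oncology nurses". Part of the programme is tailored. The nurse reviews the patient's diary, judges the prescription and the side-effect management, teaches adjustment, and revises the plan at later contacts.
- **Allocation.** Under Random assignment, patients are allocated 1:1, stratified by site. The nurse is not a unit of randomisation.
- **Data collection.** "In the IG, data are collected by the IN", whereas a research assistant does this in the control group. The values come from diaries and questionnaires that patients and family caregivers complete themselves.
- **Sample size.** The basis is "a maximum mean alleviation of 0.99 NRS (0–10) for average pain" from the pilot study, with "an alpha error of 0.05 (95%) and a beta error of 0.2 (80%) would require a 136-patient sample". This is raised to 210 for 35% attrition. No ICC, design effect or other clustering allowance is mentioned.
- **Analysis.** Aims 1 and 2 use generalized linear mixed models. For aim 1 the article adds: "This approach allows calculation of the main group and time effects, and of group-by-time interaction". The random effects are not described. The covariates listed under Quantitative data: variables and measurement are clinical and demographic; the nurse is not among them.
- **Intended use.** The Discussion paragraph of the abstract looks beyond these four people: "specially trained oncology nurses in outpatient clinics could apply the intervention to reduce side effects".

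**The concern.** In an individually randomised trial whose treatment is delivered by a few therapists in one arm, patients of the same therapist can resemble each other in outcome. The intervention-arm mean then carries a between-nurse component that shrinks with the number of nurses, here four, and not with the number of patients. Stratifying by site does not remove it, because the component exists in one arm only.

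Two things are at stake. First, if the fitted model has no nurse term, one or two unusually effective nurses could produce a significant group or group-by-time effect that is read as efficacy of the programme. This can affect any outcome that clusters by nurse, including side effects and knowledge. Second, the 80% power for the pain endpoints holds only if there is no such clustering.

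**Working it through.** **Inputs from the article:** 136 evaluable patients, alpha 0.05, power 80%, difference 0.99 NRS points, attrition 35%, 1:1 allocation, four nurses.

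**Assumptions, because the article does not give these:** a two-sided test; equal total SD in both arms; intervention patients shared evenly among the nurses, one nurse per patient; a single end-of-study comparison; nurse ICC of 0.01, 0.05 or 0.10.

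**Step 1: the plan's own figures.** 136/(1 − 0.35) = 209.2, rounded up to 210. Attrition accounts for the whole increase. The 136 cannot be reproduced independently because no SD is stated. Solving for it with 68 per arm: SD = 0.99/[(1.960 + 0.842) × √(2/68)] = 2.06, a standardised difference of 0.48. This is what an ordinary comparison of independent patients would give.

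**Step 2: variance with nesting in one arm.** With 68/4 = 17 evaluable patients per nurse, the design effect in the intervention arm is DE = 1 + (17 − 1) × ICC. The variance of the arm difference is inflated by (DE + 1)/2.

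**Step 3: consequences.**

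- SE ratio R = √[(DE + 1)/2]
- Type I error of an analysis ignoring nurse = 2 × [1 − Φ(1.960/R)]
- Power with the correct SE = Φ(2.802/R − 1.960)

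| ICC | DE | Variance inflation | R | Type I error | Power |
|---|---|---|---|---|---|
| 0 | 1.00 | 1.00 | 1.00 | 5.0% | 80% |
| 0.01 | 1.16 | 1.08 | 1.04 | 5.9% | 77% |
| 0.05 | 1.80 | 1.40 | 1.18 | 9.8% | 66% |
| 0.10 | 2.60 | 1.80 | 1.34 | 14.4% | 55% |

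**Step 4: cross-check.** A simulation of the same layout (20,000 runs, four nurses with 17 patients each against 68 independent controls) gave false-positive rates of 5.7%, 9.9% and 14.1% at ICC 0.01, 0.05 and 0.10 when nurse was ignored. A partially nested test with Satterthwaite degrees of freedom stayed between 5.2% and 5.8% over ICCs from 0 to 0.10.

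**Step 5: price of the small-sample test.** With four nurses that test has few degrees of freedom: about 11.5 at ICC 0 and 7.2 at ICC 0.05. Its simulated power was 72% at ICC 0, 68% at 0.01, 55% at 0.05 and 44% at 0.10. It costs power even when nurses do not differ, which bears on whether it should be the primary analysis.

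**The case against.** The strongest objection is that silence in a condensed article is not a stated error. A reader might infer that the mixed model treats patients of the same nurse as independent. The text does not support that: it describes no random effects at all, whether for patient, site or nurse, and that detail may sit in a full protocol or analysis plan that is not shown. The nurse's absence from the covariate list says nothing about random effects. This stands, and the point is therefore limited to no nurse effect being named.

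A reader might also conclude that the error bars are too narrow and the power overstated as a matter of fact. Both depend on an ICC the article does not give; at 0.01 the power loss is about 3 percentage points. Common training, structured components, and audio review until 95% protocol adherence is reached should hold nurse variation down. They do not show that it is zero for tailored coaching, and after that threshold recordings are only reviewed at random.

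Three further limits stand:

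- The 80% concerns average and worst pain, which are secondary in this sub-study. The power figures do not describe its primary outcomes.
- Nurses collect the data but do not rate the outcomes, and no passage says that one nurse follows a patient throughout.
- If data collection itself induced clustering, control patients could cluster by research assistant, which a model treating them as singletons would miss.

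Inference conditional on the four nurses studied is also a recognised choice for an efficacy trial, and a variance estimated from four nurses is imprecise. This is a good reason not to insist on a new primary model. It does not remove the need to say which inference is meant, given the use the abstract foresees.

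**Conclusion.** The point holds in a limited form. The design is partially nested, the sample size states no allowance for it (a design effect hidden in the unstated SD cannot be excluded, but nothing suggests one), and no nurse effect is named in the analysis. Under the assumptions listed in the working, ignoring a nurse ICC of 0.01 to 0.10 raises type I error to about 6% to 14%, and allowing for it lowers power for the pain endpoints to about 77% to 55%. At an ICC of 0 there is no inflation of type I error and the 80% stands. These figures describe a single end-of-study comparison, so for the repeated-measures model they indicate scale only. They do not show that the trial's main analysis is invalid.

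**What to change.** 1. **Data analysis, aims 1 and 2.** Name a sensitivity analysis with the nurse as a random effect in the intervention arm only, usual-care patients as singletons, and Satterthwaite degrees of freedom. Report results by nurse. If the main analysis has no nurse term, state that its inference is conditional on these four nurses.
2. **Sample size determination.** State that 80% power assumes no nurse clustering. Give the range for assumed ICCs of 0.01 to 0.10 (about 77% to 55%), labelled as assumption-based and as applying to the pain endpoints.

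The cost is wording and one additional model. The delivering nurse should be identifiable, since each session is audio recorded by the nurse who provides it. The downside is a wider interval in the sensitivity analysis and an imprecise nurse variance with only four nurses. No extra patients are requested, and adding them under the same four nurses would be inefficient: restoring 80% by the normal approximation would take 148 evaluable patients at ICC 0.01, 232 at 0.05 and 862 at 0.10.
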